### Post-resuscitation care

Return of spontaneous circulation will be defined as obtaining an organized rhythm and palpable pulse sustained for 20 minutes. Once an organized rhythm and palpable pulse is achieved, subjects will have their temperature taken via the tympanic route, stabilized and then be transported to the hospital. If a patient wakes up after ROSC is achieved, cooling will be discontinued; on the opposite, subjects will, if needed be intravenously administered bolus doses of sedation and analgesia for transport to the hospital. Doses of sedation and analgesia will be dictated by the institutional standard cooling protocol. The oxygen supply in the transport vehicle should be used to continue RhinoChill cooling during transport to the hospital. Normal transport procedures will be used for patients randomized to the control arm. Infusions of cold saline or cooling with cold packs will not be permitted in the pre-hospital setting for either group. Upon hospital arrival, a systemic temperature probe will be placed (i.e., bladder, arterial, rectal) and core temperature will be recorded. Systemic hypothermia on arrival at Intensive Care Unit (ICU) for both patient groups (treatment and control) will be performed as follows:

–Duration of hypothermia for at least 24 hours.

–Target temperature 33°C ± 1°C.

–Recording of core- and tympanic temperature every 15 minute during the induction period (i.e., until target temperature is reached).

–Rewarming rate at 0.2-0.5°C / hour.

–Control of post-cooling hyperthermia.

Subjects randomized to the early cooling group with the RhinoChill shall continue being cooled with the RhinoChill until systemic cooling procedures can be started. Intravenous sedation, analgesia and neuromuscular blockade (if used) should be initiated upon hospital arrival according to institutional cooling protocols. Doses should be adjusted as necessary over the course of cooling/re-warming. After the subject has been prepared with the standard hypothermia device, the RhinoChill should be turned off, but the intranasal catheters should be left in place while transitioning the subject to the standard hypothermia protocol.

Intermittent activation of the RhinoChill may be considered if the core temperature does not continue to drop via the systemic cooling method. Cooling via the RhinoChill system will be halted immediately if any adverse event related to the use of the RhinoChill develops.

For those patients in the control group, the standard cooling procedure will be started as soon as practical. Intravenous sedation, analgesia and neuromuscular blockade (if used) should be initiated upon hospital arrival according to institutional cooling protocols. Doses should be adjusted as necessary over the course of cooling/re-warming. Temperatures (tympanic and core) will be monitored periodically over the first 48 hours after hospital arrival for all patients. ECG, peripheral oxygen saturation, heart rate and blood pressure monitoring will continue throughout the acute care period. Ventilation settings should be adjusted to maintain arterial oxygen saturation 94-98% (e.g., PaO2 80–120 mmHg) and normocapnia (e.g., PaCO2 35-45 mmHg). A positive end-expiratory pressure (PEEP) level should be adjusted to reduce FiO2 below 60%, whenever possible. Electrolytes will be substituted as necessary to maintain normal ranges. Blood pressure should be kept above 65 mmHg at all times. Drops in pressure should be treated primarily with crystalloid fluids. If sufficient pressure control cannot be achieved with fluids alone, vasopressor drugs, such as adrenaline or norepinephrine, should be used. Serum blood glucose should be kept between 110 and 150 mg/dl with insulin administration. Enteral feeding will be initiated according to local guidelines.

### Data collection

Data collection concerning the cardiac arrest will include time to collapse; bystander CPR; location; time of arrival of basic and advanced life support, ALS, teams; time of emergency call; time of first emergency medical team initiated CPR, patient characteristics (i.e. gender, weight, age, comorbidities), resuscitation effort (time CPR is initiated by the first emergency medical staff, EMS, responder; time cooling initiated - if cooled; mechanical CPR, if not manual; time intravenous access obtained; first rhythm; total adrenaline/epinephrine dose; shock time, strength, and success; additional medication(s) and dose(s); time airway is secured; recurrent VF or re-arrest; time randomized; time ROSC or death declared). Also, quality of CPR, including the number and depth of chest compressions/min as well as CPR hands-off time, will be recorded whenever possible. After hospital admission, tympanic temperature; heart rate, peripheral oxygen saturation (SpO2), mean arterial pressure, end-tidal carbon dioxide (EtCO2), arterial blood gas analysis, initial ECG findings and Glasgow coma score will be recorded. Concomitant interventions (e.g., coronary angiogram, aortic balloon pump, bypass surgery, internal cardiac defibrillator placement) will also be recorded. The systemic cooling procedures, including the system used, the core temperature location, the duration and the hypothermia reversal algorithm will be recorded.

The Steering Committee has the responsibility to perform periodic and spot checks visits to monitor the progress of the clinical study. Completed Case Report Forms (CRFs) will be reviewed for completeness, compliance with the investigation plan, and appropriate device use and accountability. Case Report Forms will be provided to each site for each subject enrolled in the study. Required data concerning patient treatment and test results will be recorded on the CRFs at the time of the procedure or as soon as possible thereafter. Information recorded in the CRFs will be corroborated by data in the subject’s medical records. Completed and monitored CRFs will be uploaded on a website developed by the PI, which will be overseeing data entry and data quality management. Data on safety will be provided to the Steering Committee with regular time intervals.

The Steering Committee will review study integrity, safety and risk/benefit issues at periodic intervals throughout the study. The frequency of these reviews will be dependent upon the rate of patient enrollment and relevant safety issues. Independent analyses of serious adverse events will be performed and adjudicated if the frequency or nature of serious adverse events warrants it.

### Follow-up

Subjects treated with the RhinoChill will undergo rhinoscopic examination of the nasal cavity if it is warranted based on clinical signs of intra-nasal trauma (e.g., bleeding from the nostrils, whitening of the nose or other treatment-related observations). All patients still alive will undergo a neurological examination 72 hours after hospital admission. Neurological status will be classified using the Cerebral Performance Category (CPC) [25]. Subjects will be followed until death or at 90 days. The following data will be recorded concerning their hospital course: date/time subject wakes; date/time subject is taken off ventilator; date/time subject is discharged from ICU; date/time subject dies (if in hospital); date/time subject is discharged from hospital; discharge disposition; CPC at hospital discharge. CPC will be evaluated at 90 days through a telephone interview by an independent physician using the Glasgow Outcome Scale (GOS) and the 15D instrument. If there are difficulties in CPC-classification, the patient will be assessed by a neurologist at an out-clinic visit. Clinically significant serious adverse events will be recorded from the time ROSC is achieved through the earliest of the following three events: death, hospital discharge, or one week following admission. The nature and severity of the adverse event, the relationship to the RhinoChill Device, management and outcome will be recorded on the CRF.

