### Study treatment

The resuscitation attempt will follow current guidelines [24] to the greatest extent possible. After airway management (i.e. laryngeal mask or intubation), patients are randomized to early cooling or standard care. In patients randomized to early cooling, the RhinoChill catheters should be placed and cooling initiated immediately. To place the nasal catheters and start cooling takes approximately 1 minute. Cooling should be performed with the oxygen flow set to 40 L/min. There should be no changes to the care received by patients randomized to the control arm. Resuscitation attempts should be continued for at least 30 minutes after EMS arrive on the scene in all patients before deciding that further interventions are futile.

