### Study outcomes

The main objective of this study is to assess the impact on neurological intact survival rates at 90 days of trans-nasal IATH compared to standard treatment. Thus, the primary end-point will be the neurological intact survival rates (i.e. patients with CPC score of 1–2) at 90 days after arrest among all those admitted to the hospital.

Secondary end-points will include:

–Overall survival at 90 days among patients admitted to the hospital.

–Survival and neurological intact outcome at 90 days among all included patients.

–ROSC rate.

–Survival to hospital admission.

–Proportion of patients reaching target temperature (≤ 34° Celsius) within 4 hours of call to dispatcher.

–All adverse events occurring within 24 hours of beginning ALS procedures.

–Serious adverse events (SAE) from the time of patient randomization through the first seven days of hospitalization.

Importantly, in the cases where withdraw of life support is decided due to poor prognosis, the reasons must be clearly stated in the CRF, as well as results of neurological examination or additional tools (i.e. brain imaging, biomarkers, electroencephalography, somatosensory evoked potentials - SSEPs), which are used. No specific recommendation on post-anoxic coma prognostication has been provided in this study.

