### Data safety management

The Data Safety Monitoring Committee (DSMC) is constituted and will review data every 3 months. Given that it is expected that more than half of the patients will die at the scene or during the hospital stay, and that recurrent cardiac arrest at any time is possible with standard care, it is not considered appropriate to report every death to the DSMC as a serious adverse effect. Sites will report all SAEs that occur within 7 days of enrollment directly to DMSC. A “technical device failure” is defined as a failure of the device to perform its intended function when used in accordance with the instructions for use. Technical device failures will be recorded and evaluated for possible untoward effects on the subject. All clinically significant AEs or those that appear to be related to the use of the RhinoChill (i.e., whitening of the nose; epistaxis; mucosal irritation/dryness; para-sinus emphysema) as well as those that could potentially harm the patient (i.e., pleural effusion) will be recorded on the CRF from ROSC through the end of the cooling period.

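### Adverse-event recording on the CRF opens at ROSC, but the safety endpoints start at ALS or randomisation, so the AE endpoint cannot be fully populated for intra-arrest cooling or for patients without ROSC

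*Protocol article*

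**What the plan says.** Three sections of the protocol article set safety windows.

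- **Study outcomes** lists two safety endpoints among the secondary end-points: "All adverse events occurring within 24 hours of beginning ALS procedures" and "Serious adverse events (SAE) from the time of patient randomization through the first seven days of hospitalization".
- **Follow-up** sets the recording rule for serious events: "Clinically significant serious adverse events will be recorded from the time ROSC is achieved through the earliest of the following three events". The three closing events are death, leaving hospital, and a week after admission.
- **Data safety management** sets the CRF rule for adverse events. It covers clinically significant events, events that look device-related (such as nosebleed or nasal whitening) and potentially harmful ones. These "will be recorded on the CRF from ROSC through the end of the cooling period".
- **Data safety management** also gives a separate reporting duty: "Sites will report all SAEs that occur within 7 days of enrollment directly to DMSC". It adds that "Technical device failures will be recorded and evaluated for possible untoward effects on the subject", and, on deaths, that "it is not considered appropriate to report every death to the DSMC as a serious adverse effect".

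On timing of exposure, Study treatment places randomisation after airway management and then says: "In patients randomized to early cooling, the RhinoChill catheters should be placed and cooling initiated immediately". Under Study design, cooling continues to the end of CPR if resuscitation fails. Post-resuscitation care defines ROSC as a rhythm and pulse lasting 20 minutes.

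**The concern.** What is new in this trial is cooling during CPR. Both CRF windows open at ROSC, which comes after the catheters are in and the coolant is running. For a patient who never regains circulation they do not open at all. The endpoints, by contrast, start at ALS or at randomisation and so include that period and those patients. A site that follows the recording rules correctly would leave the endpoint data incomplete.

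The part at stake is mainly the non-serious device effects that the protocol itself names. Their only stated recording window starts at ROSC.

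ROSC rate is itself a secondary endpoint. With recording tied to ROSC, an AE rate over all randomised patients would count unrecorded events as absent, and a rate over ROSC patients only would condition on something that happens after randomisation. Neither is the quantity that Study outcomes defines. Minor intra-arrest events that are not written down at the scene are unlikely to be recovered reliably later.

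**Working it through.** **Step 1: the windows side by side**

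| Rule (section) | Start | End | Events covered |
|---|---|---|---|
| AE endpoint (Study outcomes) | ALS start | 24 hours later | all AEs |
| AE recording on CRF (Data safety management) | ROSC | end of cooling | clinically significant, device-related or potentially harmful AEs |
| SAE endpoint (Study outcomes) | randomisation | first seven hospital days | SAEs |
| SAE recording (Follow-up) | ROSC | earliest of death, discharge, one week after admission | clinically significant SAEs |
| SAE reporting to the safety committee (Data safety management) | enrolment | 7 days | all SAEs |

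*Start.* Both ROSC-based rules open later than the endpoint they should feed. The committee route is the only event-reporting rule that opens early enough, and it covers SAEs only.

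*End, AEs.* The end of cooling is not the same as 24 hours from ALS. Post-resuscitation care asks for at least 24 hours of systemic hypothermia, so on that reading the window usually runs past the endpoint. It closes early if cooling is discontinued because the patient wakes, or if the cooling period means device cooling only. In the latter case it has no meaning for controls.

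*End, SAEs.* The three ends differ in wording but largely coincide in practice. The SAE conflict is mainly about the start. For patients never admitted, a window counted in hospital days has no defined end.

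**Step 2: the plan's sample size, to confirm the ROSC assumption behind it**

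Inputs (Statistical analysis): 150 admitted patients per arm, ROSC around 40%, 10% lost to follow-up, 418 per arm, 836 in total.

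- 150 / 0.40 = 375
- 375 / (1 − 0.10) = 416.7, rounded up to 417 per arm

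This agrees with the stated 418 to within one patient, so 40% is the rate that the plan uses.

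**Step 3: patients with no open CRF event window**

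- Without ROSC, per arm: 418 × (1 − 0.40) = 250.8, about 251
- Without ROSC, both arms: 836 × 0.60 = 501.6, about 502
- With ROSC, per arm: 418 × 0.40 = 167.2, about 167. In the cooling arm these patients have a window after ROSC but none for the intra-arrest minutes.

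**Step 4: sensitivity to the ROSC rate**

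The 40% is a planning figure. Background says that fewer than 50% of victims achieve ROSC, and 20% or less in rural areas or with non-shockable rhythms. Taking those two figures as limits:

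- ROSC 50%: 418 × 0.50 = 209 per arm without a window
- ROSC 20%: 418 × 0.80 = 334.4, about 334 per arm

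The conclusion holds across this range. No sample-size or error-rate figure changes.

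**The case against.** The strongest reply is that the protocol does not ignore harm before ROSC. Much of that reply stands.

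- **Serious events have a route.** A reader might infer that all harms in the 60% or so without ROSC go uncaptured, or that a serious catheter injury or bleed before ROSC would never reach the safety committee. The documents do not support this. The reporting duty in Data safety management runs from enrolment and carries no ROSC condition. Device failures are also recorded without a ROSC start.
- **Interference with resuscitation is partly visible.** Data collection includes compression rate and depth and hands-off time (where possible), re-arrest, and the time of ROSC or death. A CRF is provided for every enrolled patient. ROSC rate and survival to admission are endpoints.
- **Deaths are not hidden.** A reader might take the sentence on deaths to mean that mortality is kept from the committee. It says only that not every death is reported as a serious adverse effect, and it gives a reason. The committee reviews data every 3 months. How deaths are tabulated for it can be left to a charter or the full protocol.
- **No ROSC-only denominator is stated.** A reader might infer one from the recording rule, but no section sets it, and Statistical analysis specifies intention-to-treat.
- **The SAE end points can be read together.** Seven hospital days can be taken to stop at discharge, as Follow-up does.

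This does not remove the core. The committee route covers serious events only, so non-serious events before or without ROSC have no stated window anywhere. For SAEs, sites have one rule for the committee, a later-opening one under Follow-up, and an endpoint that matches neither exactly. Nor can this be put down to a condensed article: the conflicting rules are all printed in it.

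**Conclusion.** The point holds as an internal contradiction. The safety endpoints start at ALS or randomisation, while CRF recording starts at ROSC. If the CRF rules govern:

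- Non-serious AEs during intra-arrest cooling, and in patients without ROSC, have no recording window, so the AE endpoint cannot be fully populated. This is the firmest part.
- SAEs in the same period have the separate committee route but no CRF window, so the SAE endpoint would depend on a source outside the stated recording rule.

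The size is about 251 of 418 patients per arm without ROSC, plus the intra-arrest period for the roughly 167 others in the cooling arm. It rests on the planning ROSC rate of around 40%, not on an observed rate, and on reading the ROSC start literally. It counts patients without an open window, not harms missed; the documents give no event rate from which to estimate those. The primary endpoint, sample size and error rates are unaffected.

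**What to change.** Reconcile Follow-up, Study outcomes and Data safety management:

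1. Start CRF recording of AEs and SAEs no later than the endpoints do (ALS start for AEs, randomisation for SAEs), in all randomised patients of both arms, including those without ROSC.
2. End each window at one stated point that matches its endpoint, and say what that point is for patients never admitted.
3. Make the scope of recorded events agree with the endpoint wording (all AEs, or the narrower set), and say how SAE reports to the safety committee relate to the CRF.
4. Report both endpoints by arm with all randomised patients as denominator.

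The cost is a wording change in three sections, a short AE section in the pre-hospital CRF and a little extra data entry. Following SAEs past discharge, or prescribing death tables for the safety committee, is not needed to resolve the contradiction.

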### Study outcomes

The main objective of this study is to assess the impact on neurological intact survival rates at 90 days of trans-nasal IATH compared to standard treatment. Thus, the primary end-point will be the neurological intact survival rates (i.e. patients with CPC score of 1–2) at 90 days after arrest among all those admitted to the hospital.

Secondary end-points will include:

–Overall survival at 90 days among patients admitted to the hospital.

–Survival and neurological intact outcome at 90 days among all included patients.

–ROSC rate.

–Survival to hospital admission.

–Proportion of patients reaching target temperature (≤ 34° Celsius) within 4 hours of call to dispatcher.

–All adverse events occurring within 24 hours of beginning ALS procedures.

–Serious adverse events (SAE) from the time of patient randomization through the first seven days of hospitalization.

Importantly, in the cases where withdraw of life support is decided due to poor prognosis, the reasons must be clearly stated in the CRF, as well as results of neurological examination or additional tools (i.e. brain imaging, biomarkers, electroencephalography, somatosensory evoked potentials - SSEPs), which are used. No specific recommendation on post-anoxic coma prognostication has been provided in this study.

### Statistical analysis

The primary outcome measure of this study is neurological intact survival at 90 days among all patients admitted to the hospital. Considering data from the previous trial [23], we postulated that the using of IATH with TNEC technique could improve this primary outcome from 21% to 37%. For a 80% power and α error of 0.05, the study requires 150 patients admitted to the hospital who should be randomized in each arm: however, considering a ROSC rate around 40% and 10% of lost to follow-up, the study will require a sample size of 418 patients for each arm (836 in total), regardless of initial rhythm. Analysis of data will be based on “Intention-to-treat”. A first interim analysis will be performed after 200 patients; conditional power for meeting the primary endpoint will be, if needed, recalculated at that time, and if the interim results do not correspond to the primary end-point, termination of the study for futility will be considered. In case of sample calculation exceeding 500 patients, other potential recruiting centers will be included in the study. Other interim analyses will be performed each 200 patients included. Early stopping for efficacy reasons will only be considered if major outcome differences are seen between the groups according to the Haybittle rule with a p-value ≤ 0.001.

Stratified analyses will be performed for patients whose first recorded rhythm is VF/VT versus those in whom the first recorded rhythm is PEA/asystole. Sub-group analyses will be performed for subjects where CPR was initiated within 10 minutes by a first EMS response team or where cooling was started within 15 minutes. The study is expected to last until 2016.

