TNEC is a method that has been developed to rapidly induce IATH and achieve hypothermia for human CA. The technique takes advantage of the nose as a natural orifice into the head to overcome the obstacle of cooling through the skull. The upper nasal pathways provide a large diffuse surface area and vascularity that is in close proximity to the cerebral circulation. Cooling in the nasopharynx also offers the ability to cool via direct conductive mechanisms that do not rely on spontaneous circulation [22]. In the only randomized study using such approach to induce IATH [23], 200 OHCA patients were randomized during CPR, irrespective of their rhythm, to receive either TNEC or standard of care (including post-ROSC cooling at hospital). This feasibility study showed that the method was safe for pre-hospital use. Overall survival rates were similar in the two groups (15% vs. 13%). Among patients admitted to the hospital, overall survival to hospital discharge was improved, although not significantly, during IATH (44% vs. 31%, p = 0.16). In the post-hoc analysis, the sub-group of patients with time to CPR less than 10 minutes had an increased survival rate when treated by IATH (56% vs. 29%, p = 0.04). Also, TNEC increased, although not significantly (p = 0.14), the intact neurological outcome rate from 21% to 34% when compared to the control group; these beneficial effects were more pronounced in the subgroup of patients with time to CPR less than 10 minutes (43% vs. 17%, p = 0.03).

Given these supportive data, we are conducting a randomized controlled trial comparing TNEC to conventional post-ROSC cooling. The aim is to determine whether TNEC used during CPR would improve neurological outcome in patients being resuscitated from OHCA and with a time to CPR less than 15 minutes.

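### The primary endpoint counts only patients admitted to hospital, a group formed after randomisation and after intra-arrest cooling has begun, so the main comparison is not protected by randomisation

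*Protocol article*

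**What the plan says.** The primary population is fixed in three places of the protocol article: the Abstract, Study outcomes ("at 90 days after arrest among all those admitted to the hospital") and Statistical analysis ("The primary outcome measure of this study is neurological intact survival at 90 days among all patients admitted to the hospital"). Statistical analysis also says "Analysis of data will be based on “Intention-to-treat".

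On timing, Study treatment says "After airway management (i.e. laryngeal mask or intubation), patients are randomized to early cooling or standard care", and for the cooling arm that "the RhinoChill catheters should be placed and cooling initiated immediately". Study design adds that cooling stops at the end of CPR when resuscitation fails. Both allocation and the start of treatment therefore precede admission.

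Study outcomes lists as secondary endpoints the ROSC rate, survival to hospital admission, and "Survival and neurological intact outcome at 90 days among all included patients". The aim, at the end of the Background, concerns neurological outcome in patients being resuscitated from OHCA with a time to CPR below 15 minutes.

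The sample size assumes 21% against 37% intact survival among admitted patients, 150 admitted per arm, one ROSC rate of about 40% for both arms and 10% loss. This gives 418 randomised per arm. Conditional power for futility is tied to the primary endpoint.

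**The concern.** Randomisation makes the arms comparable at the moment of allocation. It does not make the subsets who later reach hospital comparable unless treatment has no influence on who reaches hospital. Here the treatment is given during the arrest, before ROSC, so an influence is possible, and the trial measures it as an outcome. EMS crews are also unblinded and decide when to end an unsuccessful attempt once the protocol's minimum duration has passed.

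If fewer cooled patients are admitted and those missing would not have survived intact, the admitted-only rate rises in the cooling arm with no extra intact survivor. If cooling brings more patients with a poor prognosis to hospital, the rate falls, and a real gain could be hidden or harm declared. The trial's main conclusion and its futility look would carry this distortion.

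**Working it through.** **1. The plan's own figures.** Inputs from Statistical analysis: 21% vs 37%, 80% power, alpha 0.05 (taken as two-sided).

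n = [1.96·√(2·0.29·0.71) + 0.8416·√(0.21·0.79 + 0.37·0.63)]² / 0.16² = (1.2577 + 0.5316)² / 0.0256 = 125.1, so 126 per arm, or 138 with continuity correction. The stated 150 is larger and gives 86.7% power. The second step reproduces: 150 / (0.40 × 0.90) = 417, against 418 stated. The point made here does not depend on the 126 vs 150 difference.

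**2. Share excluded.** Using the planned 40% as the admission rate, 1 − 0.40 = 60% of randomised patients are outside the primary comparison.

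**3. Bias scenarios (assumed admission rates).** Intact survival per randomised patient is held at 0.40 × 21% = 8.4% in both arms, so there is no true effect. Control admission is 40%. Evaluable patients per arm are 418 × 0.9 = 376. The admitted-only rate is 8.4% divided by the admission rate. The test is the two-sided pooled z-test.

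Worked case, 30% admission with cooling: 112.8 vs 150.4 admitted, rates 28.0% vs 21.0%, pooled rate 24.0%, null SE 0.0532, alternative SE 0.0538. P(false benefit) = Φ[(0.070 − 1.96 × 0.0532) / 0.0538] = Φ(−0.64) = 26%.

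| Admission, cooling vs control | Admitted-only rates | False benefit | False harm |
|---|---|---|---|
| 30% vs 40% | 28.0% vs 21.0% | 26% | 0.1% |
| 35% vs 40% | 24.0% vs 21.0% | 9% | 0.5% |
| 40% vs 40% | 21.0% vs 21.0% | 2.5% | 2.5% |
| 45% vs 40% | 18.7% vs 21.0% | 0.7% | about 7% (7.6% by this formula, 7.3% by exact binomial) |
| 50% vs 40% | 16.8% vs 21.0% | 0.2% | 17% |

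**4. The earlier trial (Background).** Survival was 15% vs 13% of all patients, and 44% vs 31% of those admitted. The implied admission rates are 15/44 = 34% and 13/31 = 42% (33-36% and 40-44% allowing for rounding). Intact outcome of 34% vs 21% among admitted becomes 0.34 × 0.341 = 11.6% vs 0.21 × 0.419 = 8.8% of all randomised: a 13-point difference shrinks to 2.8 points. Had admission been 42% in both arms, 13 points among admitted would have been about 5 points overall. Assuming 100 patients per arm (only the total of 200 is given), 34 vs 42 admitted has p = 0.24, and the 8-point gap has a 95% interval of about −5 to +21 points.

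**5. All randomised patients as denominator.** With 40% admission in both arms, the rates are 8.4% and 0.40 × 37% = 14.8%. At 418 per arm: Φ[(0.064 − 1.96 × 0.02215) / 0.02204] = Φ(0.93) = 82.5%. If 10% of admitted patients are lost, n = 418 × (1 − 0.04) = 401 and power is 80.9%. If 10% of everyone is lost, n = 376 and power is 78.4%.

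If admission is instead 34% vs 42%, with 37% vs 21% intact among admitted, the rates are 12.6% vs 8.8%, and power at 418 is Φ[(0.0381 − 1.96 × 0.02139) / 0.02135] = Φ(−0.18) = 43%.

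**The case against.** **An effect on admission is not documented as expected.** This stands. The experimental TNEC result in the Background compares TNEC with intra-arrest cold fluids, not with standard care. The human series cited there is retrospective and used cold fluids. Listing ROSC and admission as secondary endpoints shows that they will be measured, not that a change is foreseen, and the sample size uses one ROSC rate for both arms. A reader might infer that the protocol predicts different admission rates; it does not. A possible effect is enough, however, to remove the protection of randomisation.

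**The earlier trial does not prove distortion.** This also stands. A reader might infer that the filter created its apparent benefit. The admission rates are back-calculated from rounded percentages, no time point is given for the 15% vs 13%, and the gap is compatible with chance. The implied counts (15/34 vs 13/42) give p = 0.24 by chi-square or 0.34 by Fisher's test, not the reported 0.16, so the reconstruction is only approximate.

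**Intention-to-treat may mean analysis by assigned arm within the stated population.** The article does not define the term, so a flat contradiction cannot be claimed. An admitted-only denominator still does not give what the principle is meant to secure.

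**The all-included outcome, ROSC and admission are already secondary endpoints.** They would let a reader see a distortion. They do not change which result decides the trial.

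**Changing the denominator costs power.** It does, by a limited amount under the protocol's own rates and by much more if fewer cooled patients are admitted.

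**Conclusion.** The concern holds as a design weakness of the primary endpoint, and it should be fixed because the trial's main conclusion rests on it. The population is set explicitly, so this is not a detail left to an analysis plan.

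The size depends on an unknown: how far cooling shifts admission. A 5-point shift with no change in intact survivors raises the error on one side from 2.5% to about 7-9%, and a 10-point shift raises it to 17-26%. With no effect on admission there is no such bias. These are assumed scenarios in which every patient gained or lost at admission is a non-intact one. They should not be read as the trial's actual error rate, nor as evidence that the bias runs in one particular direction.

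**What to change.** Make CPC 1-2 at 90 days among all randomised patients the primary endpoint, with patients not admitted counted as failures, and use it for the interim futility and efficacy looks. Keep the admitted-only result as a secondary endpoint, labelled as conditional on a post-randomisation event.

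Restate the planning rates as 8.4% vs 14.8%, with 40% admission in both arms given as an assumption. State that 418 per arm then gives about 78-83% power depending on loss to follow-up, and that power is lower if admission is lower with TNEC (about 43% at 34% vs 42% admission with 37% vs 21% intact).

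**Cost.** The outcome is already planned as a secondary endpoint, so no new data are needed. Power falls from about 87% to about 78-83% under the planning rates. Holding 80% power with 10% of all randomised patients lost would need 436 per arm (392 / 0.90) instead of 418. The conditional-power calculation must be redone on the new endpoint.
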